### Temperature sensation

Assessment of temperature sensation as a binary outcome (cold/warmth) will be used to evaluate regeneration of nerve function [18]. The ability to discriminate between warm and cold stimuli is tested by gently applying a cold or heated aluminum spatula to the skin, distal to the injury. The spatulas have been heated or cooled using water of different temperatures. Sensation is often compromised after a nerve injury.

### Sharp/dull

The ability to distinguish between sharp and dull is often compromised after a nerve injury. This test is used to evaluate the return of sensibility.

Sharpness is tested with a safety pin lightly pressed against the fingertip, and dullness is tested with a cotton swab gently rubbed over the fingertip, distal to the site of injury [19]. A dull or sharp sensation is registered as a binary outcome.

### Mini Sollerman test

The Mini Sollerman test assesses hand function and dexterity and is conducted on both hands [20, 21]. It includes activities that incorporate various hand grips and hand function; picking up coins, handling screw-nuts, and buttoning. Tasks within the test are assigned scores ranging from 0 to 4. The total score is then divided by 12, with higher scores indicating better hand function. The Mini Sollerman test is a widely used instrument to assess hand function and dexterity. In patients with peripheral nerve injury (median and ulnar nerve), the Mini Sollerman test has been shown to be valid [22]. The test has not been evaluated for use in outcome measurement after digital nerve injuries. The HAKIR measurement manual for nerve injuries will be used [8].

### Grip strength

Grip strength is assessed using a Jamar dynamometer® [23]. The mean of three measurements will be presented in kilograms for both hands and as a percentage of the uninjured hand. Grip strength is often negatively affected by finger injuries and is commonly measured using this instrument. Jamar® has been shown to be reliable [15] and valid [23]. The HAKIR measurements manual will be adhered to [16].

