**Assessments**								
Distance Injury—fingertip (mm)		X						
S2PD (mm)		X		X	X	X	X	
AROM (degrees)				X	X	X	X	
SWM (filament)				X	X	X	X	
Temperature (cold/warmth)				X	X	X	X	
Sharp/Dull				X	X	X	X	
Mini Sollerman test (points)				X	X	X	X	
Grip strength (kg) + VAS (0–10)				X	X	X	X	
Key pinch (kg) + VAS (0–10)				X	X	X	X	

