### Active range of motion (AROM)

The range of motion of finger joints will be measured as degrees of motion in MCP, PIP, and distal interphalangeal (DIP) joints. A finger Goniometer will be used for measurements [14, 15] and the degrees of motion of the three finger joints will be summed. The injured finger and the corresponding finger on the uninjured hand will be measured. The measurement technique will adhere to the Swedish hand surgery quality registry (HAKIR) measurement manual [16]. Finger stiffness is a common complication of any finger injury.

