### Key pinch

Key pinch, thumb tip pressed against the middle phalanx of the index finger, is used to measure strength and assessed by a pinch gauge [16, 23]. It will be recorded for both hands, and the mean of three measurements will be presented in kilograms, and as a percentage of the uninjured hand. Key pinch is often negatively affected by finger injuries and is commonly measured using this instrument. This test has also been shown to be reliable [23].

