## Statistical methods

### Statistical methods for primary and secondary outcomes {20a}

Primary outcome is a dichotomous outcome that will be presented as proportions of patients obtaining return of 2PD < 10 mm 1 year after injury, presented with 95% confidence interval, and proportions between groups will be compared with Chi^2^ analysis.

All numerical values will be tested for normality by Shapiro–Wilk’s test.

We assume normality/parametric data for age, AROM, and grip strength. Results are presented as numerical values on an interval scale. Central tendencies of data will be described as means with their corresponding standard deviation, and comparisons between groups will be performed with Student’s *t*-test or repeated measures ANOVA.

Categorical data will be presented as proportions and compared by Chi^2^ analysis, unless Fisher’s exact test is demanded due to expected small numbers. Ordinal data will be presented as medians and interquartile range (IQR), and Mann–Whitney *U*-tests or Wilcoxon’s test used for comparisons between groups.

We assume a skewed distribution for time to injury, sick leave, and PROMs, which will be presented as medians with IQRs and compared by Mann–Whitney *U*-tests or Wilcoxon’s test.

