### Methods for additional analyses (e.g. subgroup analyses) {20b}

The primary outcome will be analyzed with mixed models effects, taking possible confounders into account, such as age (years), gender (female/male), smoking (yes/no), handedness (left/right), injury mechanism, level of injury (proximal/middle phalanx), distance from injury to fingertip (mm), time from injury to operation/immobilization (days). No other additional or subgroup analyses are planned.

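### Grip strength and AROM are compared between arms without adjusting for the uninjured side, although it is measured, so secondary outcomes lose precision

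*Protocol article*

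**What the plan says.** Three outcome sections of the protocol article plan a measurement on the uninjured side.

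- **Grip strength:** "The mean of three measurements will be presented in kilograms for both hands and as a percentage of the uninjured hand".
- **Key pinch:** both hands are recorded, and the result is shown in kilograms and "as a percentage of the uninjured hand".
- **AROM:** "The injured finger and the corresponding finger on the uninjured hand will be measured". No percentage or side-to-side difference is defined.

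Table 1 places all three at 3 weeks and at 3, 6 and 12 months, with nothing at enrolment or allocation.

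The analysis is in Statistical methods for primary and secondary outcomes {20a}: "We assume normality/parametric data for age, AROM, and grip strength", and "comparisons between groups will be performed with Student’s *t*-test or repeated measures ANOVA". No covariate is named, and key pinch is not in that list. Under Methods for additional analyses {20b}, "The primary outcome will be analyzed with mixed models effects, taking possible confounders into account". The covariates listed there do not include the uninjured side, and the section closes by ruling out further additional analyses.

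**The concern.** Grip and pinch in kilograms carry the variation between people in sex, body size and age. In a two-sample comparison all of it goes into the standard error. The opposite hand of the same patient captures much of that variation and is already to be measured, yet no planned comparison uses it as a covariate.

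The percentage removes part of this variation but adds noise from its denominator. For AROM not even a percentage is defined. Section {20a} also does not say whether kilograms or the percentage is tested for grip.

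Range of motion and grip strength are named in the secondary objectives. The sample size was set for the binary primary outcome only, so precision on these measures depends on the analysis. At stake are wider confidence intervals than the collected data allow, and a lower chance of detecting a true difference in stiffness or strength.

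**Working it through.** **Plan's own figure.** The protocol gives no standard deviation, detectable difference or power for grip, pinch or AROM, so there is nothing to reproduce for these outcomes. The only input taken from it is the evaluable sample: 150 patients in 1:1 allocation, i.e. 75 per arm, with a two-sided 0.05 level (Sample size {14}; Trial design {8}).

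**Assumed inputs.** The correlation rho between the injured-side and uninjured-side values is not in the protocol. It is varied from 0.3 to 0.9.

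**Formulas.**

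- Residual variance after adjustment = (1 − rho²) × unadjusted variance, so the standard error ratio is √(1 − rho²).
- Difference detectable with 80% power, in SD units = (1.960 + 0.842) × √(2/75) × √(1 − rho²). Unadjusted: 2.802 × 0.1633 = 0.457 SD.
- Power for a 0.4 SD difference = Φ(0.4 / (0.1633 × √(1 − rho²)) − 1.960). Unadjusted: Φ(2.449 − 1.960) = Φ(0.489) = 69%.

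| rho (assumed) | 1 − rho² | SE ratio | SE reduction | Detectable difference (SD) | Power at 0.4 SD |
|---|---|---|---|---|---|
| no adjustment | 1 | 1 | – | 0.457 | 69% |
| 0.3 | 0.91 | 0.95 | 5% | 0.436 | 73% |
| 0.5 | 0.75 | 0.87 | 13% | 0.396 | 81% |
| 0.6 | 0.64 | 0.80 | 20% | 0.366 | 86% |
| 0.7 | 0.51 | 0.71 | 29% | 0.327 | 93% |
| 0.8 | 0.36 | 0.60 | 40% | 0.274 | 98% |
| 0.9 | 0.19 | 0.44 | 56% | 0.199 | >99% |

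**Is the percentage a substitute?** This was simulated for grip only, with 75 per arm and 3000 trials per correlation. The inputs are all assumed: means of 36 kg (injured) and 40 kg (uninjured), SD 12 kg, true difference 3 kg (3/12 = 0.25 SD).

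| rho | t-test, kg | t-test, percentage | Adjusted |
|---|---|---|---|
| 0.3 | 31% | 20% | 34% |
| 0.5 | 33% | 29% | 43% |
| 0.6 | 33% | 34% | 47% |
| 0.7 | 34% | 42% | 57% |
| 0.8 | 34% | 62% | 72% |
| 0.9 | 33% | 88% | 94% |

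The formula agrees. Unadjusted power is Φ(0.25/0.1633 − 1.960) = Φ(−0.43) = 33%. Adjusted power at rho 0.6 is Φ(0.25/(0.1633 × 0.80) − 1.960) = Φ(−0.05) = 48%. A separate run of 4000 trials at rho 0.6 to 0.9 agreed to within about 4 percentage points.

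A second scenario (coefficient of variation 30%, effect 10% of the mean, also assumed) gave the same ordering. At rho 0.3, 0.5, 0.7 and 0.8, adjusted power was 71%, 79%, 92% and 98%, against 66–67% for kilograms and 35%, 48%, 73% and 88% for the percentage. Type I error was 4–6% for all three methods.

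Adjustment had the highest power at every correlation tried. The percentage did worse than raw kilograms at rho of 0.5 or below.

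**The case against.** The strongest reply is that nothing here is an error. In a randomised trial an unadjusted comparison is valid and unbiased, and covariates for secondary outcomes are ordinarily left to an analysis plan. The first half stands. The second does not fully answer the point: the protocol names the tests, confines the adjusted model to the primary outcome and rules out other additional analyses, so the unadjusted comparison is a stated choice.

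Five further objections stand in part.

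- **The plan is not a t-test alone.** Repeated measures ANOVA is the named alternative. As written, it does not use the uninjured side either, so the gap remains.
- **Grip and pinch may be compared as percentages.** Section {20a} does not say which scale is tested. If it is the percentage, the gain from adjustment is smaller at high correlation (88% to 94% power at 0.9 above), but the percentage can also be worse than kilograms.
- **All magnitudes rest on assumptions.** The correlation, SD, means and effect are absent from the protocol. The power simulation covers grip only, and the correlation for AROM may be quite different.
- **Adjustment is not free.** The first uninjured-side value comes 3 weeks after randomisation. With no imputation planned ({20c}), a patient without that value would drop out of a model that insisted on it.
- **Dominance is not always defined.** Handedness is recorded with an ambidextrous category, so injury to the dominant hand needs a rule for those patients.

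A reader might also infer that these comparisons are invalid or that the trial's main conclusion is weakened. The protocol supports neither reading: randomisation protects the unadjusted comparisons from bias, and the primary outcome is a two-point discrimination proportion with its own analysis.

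**Conclusion.** The point holds as a missed gain in precision on AROM, grip strength and key pinch. The uninjured side is to be measured for all three, and no planned comparison adjusts for it. It is a worthwhile improvement of low severity, with no effect on bias, the primary outcome or the sample size.

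The loss cannot be fixed at one number. It is slight if the two sides correlate weakly and large if they correlate strongly, and the protocol gives no correlation. The power figures illustrate the ordering of the methods for grip and should not be read as this trial's power. It would also go too far to call the change costless. The covariate is legitimate only if treatment does not alter the uninjured hand. That is plausible, because both arms have the same 3-week cast and identical follow-up, but it is an assumption and should be stated.

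**What to change.** In Statistical methods {20a}, replace the t-test or ANOVA for these outcomes with one named model, along these lines:

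*AROM, grip strength and key pinch at 12 months will each be compared by linear regression of the injured-side value on treatment group, adjusted for the uninjured-side value. The adjusted mean difference will be reported with its 95% confidence interval. Percentages of the uninjured hand will be descriptive only.*

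Add three specifications:

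1. The covariate is the uninjured-side value from the 3-week visit or, if that is missing, from the earliest later visit. Both sides are due to be measured at 12 months, so a patient with a complete 12-month assessment is not lost under the no-imputation rule.
2. State the assumption that treatment does not affect the uninjured hand, with the reason given above.
3. If injury to the dominant hand is added as a covariate, give ambidextrous patients a defined category.

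The cost is a few sentences and a slightly more complex model whose covariate is measured after randomisation. No new data are needed. Completion of inclusion is anticipated at the end of 2030, so the change can be made before the final analysis.

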### Key pinch

Key pinch, thumb tip pressed against the middle phalanx of the index finger, is used to measure strength and assessed by a pinch gauge [16, 23]. It will be recorded for both hands, and the mean of three measurements will be presented in kilograms, and as a percentage of the uninjured hand. Key pinch is often negatively affected by finger injuries and is commonly measured using this instrument. This test has also been shown to be reliable [23].

### Visual Analogue Scale (VAS)

During Jamar and pinch gauge assessments, the resulting intensity of pain will be rated by the patient on a straight line marked from 0 to 10 [24]. Where 0 is “no pain” and 10 is “worst possible pain” [24]. Rates from both hands will be recorded. VAS is a common self-assessment tool used to measure perceived pain.

### Patient-reported outcome measures (PROMs)

#### Short version of the Disabilities of the Arm, Shoulder and Hand questionnaire (Quick-DASH)

The Quick-DASH questionnaire is a region-specific validated measure of the perceived disability in the upper extremities, focusing on physical activity, pain, and symptoms [25]. It consists of 11 questions, and was developed from the original DASH questionnaire, which consisted of 30 questions [25, 26]. Each question is given a score between 1 and 5. To calculate the final score, the results of all questions are summed up, divided by the number of questions answered, subtracted by 1, and multiplied by 25. The total score ranges from 0 to 100, where 100 indicates maximal perceived disability. Not more than one missing item is allowed. The minimal clinically important difference has been reported to be a difference of 15–20 [27, 28].

### The HAKIR-8 questionnaire (HQ-8)

The HQ-8 questionnaire was constructed for evaluating patient-reported outcomes after hand surgery [29] and has been used since 2010 [17]. The HQ-8 includes seven questions concerning perceived symptoms in the affected or injured hand (pain on load, pain in motion without load, pain at rest, stiffness, weakness, numbness, and cold sensitivity) and one item about the ability to perform daily activities. Items are scored on a numeric 11-point box scale (NRS11) with numerical descriptors (0, 10, 20,…0.100) indicating no or maximal symptoms. The preoperative and the postoperative questionnaires are identical, with the exception that a question about the satisfaction with the result, scored 0–100, is added postoperatively. The questionnaire was adapted for the study by adding a “Not Relevant” option to the question regarding the “operated hand,” since not all patients will be operated. Its validity has been studied and is shown to be useful as a complement to Quick-DASH after hand surgery [29].

### Hospital Anxiety and Depression Scale (HADS)

HADS aims to measure symptoms of anxiety and depression [30]. It is a self-assessment questionnaire consisting of 14 items, seven about anxiety and seven about depression. Each question is scored 0–3. If the total score exceeds 10 in either anxiety or depression items, an anxiety or depression disorder is likely to be present, and it can increase the experience of post-surgical pain [30].

### Pain Catastrophizing Scale (PCS)

The psychological ability to cope with pain differs from individual to individual. Pain catastrophizing might be a personality risk factor for post-surgical pain [31]. The PCS was developed with the aim of identifying individuals who were more susceptible to experiencing pain than others [32]. The self-reported measure includes 13 items that assess feelings of helplessness, rumination, and magnification experienced in relation to pain. Responses are scored on a scale from 0 to 4, reflecting the frequency of these experiences. The maximum score is 52. A total score > 30 represents a clinically significant level of pain catastrophizing. High scores, > 30, might be a risk factor for post-surgical pain. Elevated levels of helplessness, rumination, and magnification, as identified by the PCS, are also common in individuals with anxiety and depression, indicating a potential overlap in psychological factors contributing to pain perception [33]. The scale was validated in Swedish in 2019 [34].

### Douleur Neuropathique en 4 questions (DN4)

This questionnaire is used as a screening instrument for neuropathic pain. The DN4 has been reported to be superior in sensitivity and specificity in identifying neuropathic pain [35]. The questionnaire is composed of ten items, with seven questions designed for patient response and three for the examiner to complete. The maximum attainable score is ten, and a score of four or higher suggests the probable presence of neuropathic pain. Neuropathic pain is a dreaded complication of nerve injury and will be reported as the result of the DN4 [35]. DN4 was translated into Swedish in 2011 and had the highest accuracy compared to three other tests when comparing neuropathic pain in patients with spinal cord injury [36].

### Complications

#### Neuropathic pain/neuroma

Suturing a digital nerve is considered to reduce the risk of neuroma development. Patients with a DN4 score of ≥4 are considered to exhibit signs of neuropathic pain and will undergo further examination.

### Cold intolerance

In the DN4 questionnaire, the first question (1:2) addresses cold and pain, and so does question number 7 in the HQ-8 questionnaire. The results from these questions will be analyzed separately from the rest of the questionnaires in order to assess cold intolerance. Cold intolerance is the most common complication after digital nerve injury [37].

### Wound infection

Symptoms consistent with infection (redness, swelling, pain, pus) will be recorded as a binary outcome, “yes” or “no”. Symptoms will be treated according to local routines.

### Other outcomes

#### Demographics

Data, including age (years), perceived gender (male/female), smoking (yes/no), handedness (right/left/ambidexter), occupation, comorbidities, injury mechanism, level of injury (middle or proximal phalanx), and time from injury to operation/immobilization (days), will be collected at inclusion.

### Sick leave

Sick leave will be documented and presented as the number of work absence days from inclusion to 1-year follow-up. A prolonged absence from work could potentially be caused by complications such as neuropathic pain. This might serve as an additional indicator of possible poor outcomes.

### Participant timeline {13}

#### Sample size {14}

This study was designed as a prospective superiority trial, aiming to determine whether one treatment strategy resulted in a superior sensory recovery outcome compared to the other. The primary endpoint was the proportion of participants achieving recovery of sensibility, defined as S2PD ≤ 10 mm, measured at the 1-year follow-up.

A power calculation was performed based on the assumption of a 20% clinically meaningful difference between groups. Using a two-sided significance level of *p* < 0.05 and a statistical power of 80%, the required sample size was calculated to be 150 patients. This calculation was based on an expected outcome proportion derived from a previously published study [38]. To account for an anticipated dropout rate of 10%, the total sample size was adjusted to 166 participants.

### Recruitment {15}

Inclusion started on the 29th of August 2022. The closing date is anticipated to 31 st of December 2030. All patients seeking care in the Södersjukhuset hospital due to a suspected digital nerve injury are screened for inclusion and exclusion criteria, and all eligible patients are invited to participate. All eligible individuals who decline participation will have their reason for non-participation documented. Additionally, for participants who withdraw from the study or follow-up, their reason for withdrawal will be recorded, if possible.

## Assignment of interventions: allocation

### Sequence generation {16a}

The allocation sequence was generated using block randomization and was prepared before the start of inclusion. Each block contains 10 tickets labeled “cast” and 10 tickets labeled “operation,” except for the last block, which consists of 6 tickets (three of each), as the total number of included patients was set to 166. Each ticket in one block was then randomly put in an opaque sealed envelope labeled 1–20, 21–40, etc.

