## Trial design {8}

This is a single-center, unblinded, superiority, randomized controlled trial. The study includes patients with isolated digital nerve injuries, defined as a single digital nerve laceration without concomitant injury to flexor or extensor tendons, or to adjacent digital nerves. Patients will be randomized in a 1:1 ratio, without stratification, to either surgical nerve repair and cast, or immobilization only.

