### Implementation {16c}

The doctor examining the patient enrolls the participant. Together with the research nurse, an envelope (in consecutive order) is drawn. Either the doctor or the nurse informs the participant of the allocation.

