## Assignment of interventions: blinding

### Who will be blinded {17a}

Interventions are not blinded, neither to healthcare personnel nor the patient.

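### A constant, published block size of 20 on one open-label list lets anyone who keeps a tally foresee some allocations (on average about 16 of 166), which leaves a moderate, cheaply reduced route to selection bias

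*Protocol article*

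**What the plan says.** Trial design {8} fixes one list: "Patients will be randomized in a 1:1 ratio, without stratification". The trial has a single centre and is unblinded.

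Sequence generation {16a} fixes the block content: "Each block contains 10 tickets labeled “cast” and 10 tickets labeled “operation". The final block is the one exception: it holds 3 tickets per arm, to reach the planned 166. The section then describes the envelopes: "Each ticket in one block was then randomly put in an opaque sealed envelope labeled 1–20, 21–40, etc".

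Implementation {16c}: "The doctor examining the patient enrolls the participant. Together with the research nurse, an envelope (in consecutive order) is drawn". Who will be blinded {17a}: "Interventions are not blinded, neither to healthcare personnel nor the patient". Concealment mechanism {16b} names opaque sealed envelopes and nothing else.

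The article describes no variation in block size, no withholding of the block size from enrolling staff and no central allocation. Under {31c} it calls itself the complete protocol. According to Recruitment {15} and Trial status, inclusion began in August 2022 and is expected to run to the end of 2030, so the scheme is in print while patients are still being enrolled.

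**The concern.** An opaque envelope hides its own ticket. It does not hide a result that follows from earlier allocations and a known block total. Four features combine here: the block size never changes, there is one list, every past allocation is visible to staff, and the doctor who judges eligibility and enrols the patient is present at the draw. Towards the end of each block the next arm can be predicted, and at the very end it is known.

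Concealment exists to keep the decision to invite or enrol independent of the next arm. Section {6b} and the Discussion call surgery the gold standard, so some clinicians may prefer one arm for some patients. If foreknowledge influenced who entered a given slot, the arms would differ before treatment. Intention-to-treat analysis keeps patients in the arms they were assigned to, so it cannot undo that. The adjusted model in {20b} corrects only for the factors it measures. The Discussion does mention selection bias during recruitment, but it links this to patients' willingness to be randomised, not to predictable allocation.

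**Working it through.** **Inputs (protocol article).** Block of 20 = 10 + 10; last block of 6 = 3 + 3; total 166 ({16a}). One list, 1:1, single centre, unblinded ({8}, {17a}). Consecutive drawing ({16c}).

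**The plan's own figure.** (166 − 6)/20 = 8 full blocks, and 8 × 20 + 6 = 166. The list length is reproduced.

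**Allocations certain in advance.** Take a block with m tickets per arm. Once one arm is used up, all remaining tickets are known. The probability that at least the last k tickets are known is 2·C(2m − k, m)/C(2m, m). Summing over k = 1 to m gives an expected 2m/(m + 1).

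- m = 10: 20/11 = 1.818 per block. The last ticket is always known; the last two with probability 0.47, the last three with 0.21 and the last four with 0.09.
- m = 3: 6/4 = 1.5.
- Whole list: 8 × 1.818 + 1.5 = 16.05 of 166 (9.7%).

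Simulating 20,000 lists gave a mean of 16.1, with 95% of lists between 11 and 23. The minimum is 9, one for each of the 9 blocks.

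**Allocations predictable at 2:1 odds or better.** Exact enumeration gives 5.40 per block of 20 and 2.80 in the block of 6: 8 × 5.40 + 2.80 = 46.0 of 166 (28%).

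**Always guessing the arm with more tickets left.** The expected number of correct guesses per block is m + 2^(2m − 1)/C(2m, m) − 0.5.

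- m = 10: 10 + 524,288/184,756 − 0.5 = 12.34 of 20.
- m = 3: 3 + 32/20 − 0.5 = 4.10 of 6.
- Whole list: 8 × 12.338 + 4.10 = 102.8 of 166 (61.9%), against 83 (50%) by chance.

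**Alternatives (simulated, 166 allocations).** Shorter fixed blocks with known boundaries are worse on certainty: about 28 certain with blocks of 10, 42 with blocks of 6 and 56 with blocks of 4.

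For randomly varied blocks, assume that the tallier knows the set of possible sizes but not their order.

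| Block sizes | Certain, of 166 | Guessed right from running totals |
|---|---|---|
| Fixed 20, last 6 (plan) | 16.05 | 61.9% |
| Varied 4/6/8 | about 4 | about 68% |
| Varied 10 to 20 | about 0.5 | about 63% |
| Varied 16 to 24 | about 0.4 | about 61% |
| Simple randomisation | 0 | 50% |

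If the set of sizes is also unknown, the certain counts fall further; for 4/6/8 the count is then below 1.

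**Cost of simple randomisation.** If all 166 were allocated this way, the SD of the difference in arm sizes would be √166 = 12.9. The expected efficiency loss is (12.9/166)² = 1/166 = 0.6%. It is smaller if only part of the list is replaced.

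**The case against.** The other side has several fair points.

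- **The figure is conditional.** Sixteen is an average, and it applies only to someone who knows the block size and keeps an exact count. Enrolment is by the on-call surgeon. At 166 patients between August 2022 and December 2030 (about 8.3 years), accrual is about 20 a year, so one block lasts about a year. Rotating doctors may hold no tally. This stands as a limit on size, but the research nurse at the draw could keep a count, and the block size is published.
- **The document contains safeguards.** All eligible patients are to be invited, reasons for declining are recorded ({15}), consent comes before randomisation ({18a}), and the eligibility criteria limit how long a patient can be delayed. These narrow the route. They do not stop a foreseeable arm from influencing the judgement of eligibility or the way the trial is presented.
- **Motive is not documented.** Section {6b} also says that both approaches are regarded as possible options. A clinician's preference is plausible but is not shown.
- **Blocks of 20 are long.** Correct: shorter fixed blocks would be worse, so the exposure is moderate.

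A reader might also infer two stronger statements from {16a} and {16c}. One is that block boundaries are printed on the envelopes. The label text can equally mean single numbers 1 to 20, then 21 to 40, and consecutive drawing favours that reading. Under either reading, a known constant size reveals the boundaries. The other is that the enrolling doctor draws alone; the text has the research nurse taking part.

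**Conclusion.** The concern holds as a design weakness of moderate size; the article contains no contradiction or miscalculation on this point. For a person who knows the block size and tallies the open allocations, about 16 of 166 allocations would on average be certain over the whole list (never fewer than 9), about 46 would be predictable at 2:1 or better, and about 62% could be guessed correctly.

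These figures rest on one list used in order and a complete tally. Without a tally they do not apply. It would be tempting to conclude that the trial is already biased, but the document does not support that: it shows an opening for selection, not its use. The number of patients enrolled so far is not given, so the share of the 16 that can still be prevented is unknown. The change is worth making because it is cheap and the list is still in use.

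**What to change.** For the remaining patients, replace all unopened envelopes with a new list generated by someone who neither recruits nor treats trial patients. There are two acceptable forms:

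- **Simple randomisation.** This removes all predictability.
- **Large block sizes, varied at random and not disclosed to recruiters.** This removes nearly all certain allocations, but guessing from running totals stays at about 61 to 63%, close to the present level.

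Small varied blocks such as 4/6/8 also reduce certainty, but guessing stays near 68%, so they are the weaker choice. Shorter fixed blocks should not be used.

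Number the new envelopes singly, and write the participant's identity and the consent date on each one before it is opened. State in the protocol when the new list took effect and how many patients were allocated under each list.

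The cost is a short amendment, one new list and re-filled envelopes. Arm sizes may become slightly unequal, with an average efficiency loss of at most about 0.6% under simple randomisation. Allocations already made stay as they are.
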